### Recruitment and randomization

Recruitment procedures commenced in 2017 and will cease in 2022. In the first wave of recruitment, Unity Health Care generated a list of the names and addresses of patients across their practices who fulfilled the study’s eligibility criteria. Candidate participants received a letter describing the study, incentives for participation, contact information for whom to follow up with, and the dates and locations for the recruitment sessions. We have also relied on word-of-mouth and targeted recruitment at Unity’s practices: Unity providers supplemented recruitment efforts by handing out flyers to eligible patients. We will follow the same recruitment processes for our BMSI participants.

Recruitment sessions, which occur in both the morning and afternoon of the same day to maximize attendance, are held in local churches located in predominantly AA neighborhoods. Women are randomly assigned to attend a session designed for the treatment arm or the usual care arm. JHCHDS staff, who conduct the randomization, are blinded to which sessions are for either arm, and both receive identical recruitment sessions. Each session features two interactive presentations. The first presentation, conducted by the GPHIC, describes cardiovascular health disparities at large and the ramifications of hypertension within AA communities, and highlights core components of the PTSC program. The second presentation, given by the JHCHDS, explains the study’s goals, timelines, and data collection procedures, and walks participants through the informed consent process. Attendees learn of their assigned treatment arm after the presentations have been made. At that point, written consent to participate in the study is obtained from those who wish to be a part of the trial.

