### Baseline data collection

Upon consent, study participants complete a baseline survey composed of items measuring their health behaviors (including self-reported adherence, physical activity, and diet), psychosocial attributes (e.g., depressive symptomology, hypertension-related locus of control, and adaptive stress management techniques), perceived health status, and healthcare utilization.

Baseline measures of BP, waist circumference, height, and weight are also obtained. Blood pressure is assessed using a digital Omron 10 series device. Women are seated at rest for 5 min with their feet flat on the floor, and their arms raised at the heart level. Appropriate cuff sizes, based on each participant’s arm circumference, are attached to the device to detect their BP reading accurately.

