## Discussion

Preliminary analyses of the baseline characteristics of the study’s participants reveal.

that, thus far, a substantial portion of participants assigned to the intervention group did not receive the intervention as intended. Of the 216 women randomly assigned to the PTSC intervention, 103 received the intervention as designed (that is, they attended at least 8 of the 13 Sister Circles), while the remaining 113 did not. This indicates a need for culturally- and economically-sensitive mitigation strategies that will encourage higher receipt of the intervention. In an effort to uncover some of the factors related to low exposure to the PTSC program, we created a short survey to elicit information about why they were not participating. Two of the top 3 reasons cited for non-involvement in the study were related to the accessibility of the Sister Circles (transportation and scheduling), and the other reason was a matter of personal health (not feeling well enough to attend). These realities attest to the difficulties associated with designing and implementing a randomized trial in the real-world context of engaging with a socioeconomically vulnerable study population, whose members may be grappling with multiple comorbid conditions and various structural determinants of health. Additional analyses indicate that most of the attrition observed thus far occurred between the recruitment meeting and participants’ first Sister Circle session, despite the fact that participants meet their facilitator at the recruitment meeting, and facilitators contacted study participants in between the recruitment session and the first Sister Circle session. Bearing in mind that the reduced number of study participants exposed to the intervention threatens our ability to detect statistically significant differences between the intervention and usual care groups, and to tackle the issue of attrition prior to the first Sister Circle, we have shortened the time between the recruitment meeting and the first Sister Circle session to less than two weeks. This information informs our approach for the third cohort of participants. We will make the Sister Circle schedules more flexible, provide transportation assistance, and create protocols for facilitators to follow up with participants prior to the start of their Sister Circle. In addition, we will allow study participants assigned to the intervention to choose their Sister Circle from a menu of Sister Circles that vary by time, i.e., from a daytime, evening, and weekend Sister Circle.

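### Allocation and its disclosure precede consent, baseline and the gap in which most attrition occurred, and the planned changes leave this order in place for Baltimore; the as-randomised contrast is diluted, but a change now would recover little pooled power

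*Protocol article*

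**What the plan says.** Recruitment and randomization sets the order of events. The arm is settled before the meeting: "Women are randomly assigned to attend a session designed for the treatment arm or the usual care arm". It is disclosed there: "Attendees learn of their assigned treatment arm after the presentations have been made". Consent comes next: "At that point, written consent to participate in the study is obtained from those who wish to be a part of the trial". Measurement comes after that, as the next section states: "Upon consent, study participants complete a baseline survey". The second site copies the scheme: "We will follow the same recruitment processes for our BMSI participants".

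The Discussion reports on the 216 Unity women assigned to PTSC. Of these, 103 reached the attendance threshold of 8 circles out of 13, and 113 did not. It also locates the loss: "most of the attrition observed thus far occurred between the recruitment meeting and" the first circle. Transportation and scheduling are two of the three leading reasons given; ill health is the third. The authors themselves say that low exposure threatens their ability to detect a difference.

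Their response is that "we have shortened the time between the recruitment meeting and the first Sister Circle session to less than two weeks", with transportation help, facilitator follow-up before the first circle and, for the third cohort, a choice of times: "we will allow study participants assigned to the intervention to choose their Sister Circle from a menu of Sister Circles that vary by time". That choice is offered only after assignment.

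**The concern.** A woman who leaves between the meeting and the first circle has already been randomised. If she was assigned to PTSC, she belongs in that arm's as-randomised analysis although she never met the program. Women of the same kind are expected in usual care in the same proportion, where they cannot be identified. The result is dilution: the difference between arms shrinks towards zero.

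Allocating after the gap would let these women leave before they belong to either arm. The comparison within Baltimore would stay unbiased and be less diluted, and nobody would have to be excluded by attendance.

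The order also lets the decision to consent depend on the arm, because women hear the arm first. Moving consent and baseline ahead of disclosure closes that route in the same step. The planned measures may reduce early loss, but none of them changes when allocation happens.

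**Working it through.** **Inputs.** 216 PTSC and 125 usual care women recruited, and 100 still to come from Baltimore (Study population and eligibility criteria). 103 of 216 receivers (Discussion). 80% with high blood pressure, a 15% reduction, two-sided alpha 0.05, 308 before attrition, 440 in total (Power calculation).

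**The plan's own figure.** The power is not stated. Reading the reduction as 15 points (80% v 65%) and assuming 80% power, the two-proportion formula with continuity correction gives 151 per arm, 302 in total, within 3% of 308. A relative reading (80% v 68%) gives 418 to 450 and does not reproduce it. The absolute reading is used below.

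**Assumptions not in the article.** Non-receivers gain nothing; outcome data are complete; there is no clustering; Baltimore is allocated 1:1 and repeats Unity's losses. No count of pre-circle losses is given. I take the attrition to mean the 113 non-receivers and most to mean at least half, so 57 to 113 women.

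**Dilution as the plan stands.** Receipt = 103/216 = 47.7%. As-randomised difference = 15 × 0.477 = 7.2 points.

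**Baltimore with later allocation, lower bound of 57.** Share lost before allocation = 57/216 = 26.4%. Receipt among the rest = 103/159 = 64.8%. Baltimore difference = 15 × 0.648 = 9.7 points. This supposes that every such woman leaves before allocation.

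**Pooled difference.**
- 100 consent, no replacement: 100 × (159/216)/2 = 36.8 per arm; (216 × 7.15 + 36.8 × 9.72)/252.8 = 7.5 points.
- 100 allocated: (216 × 7.15 + 50 × 9.72)/266 = 7.6 points. Consents needed = 100/(159/216) = 136.

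**Pooled power.** Power = Φ[(d − 1.96·SE0)/SE1], where SE0 = √[p̄(1 − p̄)(1/nC + 1/nT)] and SE1 = √[pC(1 − pC)/nC + pT(1 − pT)/nT], with pC = 0.80 and pT = 0.80 − d.

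| Case | PTSC v usual care | d | SE0 | SE1 | Power |
|---|---|---|---|---|---|
| No change | 266 v 175 | 0.0715 | 0.0418 | 0.0407 | 40% |
| Later allocation, not replaced | 252.8 v 161.8 | 0.0753 | 0.0434 | 0.0422 | 41% |
| Later allocation, 100 allocated | 266 v 175 | 0.0763 | 0.0419 | 0.0408 | 44% |

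**Upper bound.** If all 113 left before the first circle, the two later-allocation cases give 7.9 points and 42%, or 8.6 points and 53%; the latter needs about 210 consents.

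**Dilution or bias?** In a simulation with never-starters at higher control risk (85% v 78%), early allocation put them in both arms equally (26% v 26%; 52% v 52%) and shrank a 15-point effect to about 11 and 7 points. Late allocation recovered about 15 points among starters. The comparison as randomised is weakened, not biased.

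**The case against.** The strongest reply is that little can still be changed. With 341 women already recruited, later allocation touches about 100 of 441, and without replacement the pooled power gain is about one point. This stands. A reader might infer a large gain by applying later allocation to the whole trial, but that trial can no longer be run.

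The authors have also acted on the causes women reported. Residual early loss in Baltimore is therefore unknown, and Unity's pattern probably sets the gain too high. This stands too. Similarly, if non-starters also miss follow-up, receipt among those analysed exceeds 47.7% and less dilution remains to remove.

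Third, the stated aim is effectiveness, and non-uptake is part of effectiveness. That is fair: the Baltimore result would describe women able to start a circle. Reporting losses before allocation keeps uptake visible.

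Three stronger readings are tempting and not supported:
- That never-starters unbalance the arms. Randomisation spreads them evenly. Bias would arise only if they were excluded, or lost outcome data, in one arm.
- That later allocation would remove all never-starters. A woman can confirm a slot and still be kept away by transport, schedule or ill health.
- That the 216 to 125 split proves arm-dependent consent. The planned 220 per group suggests 1:1, under which such a split is very unlikely (two-sided p about 1e-6), but the ratio actually used is not given. The split is compatible with arm-dependent consent and does not establish it.

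**Conclusion.** The concern holds in limited form. The arm is set before the recruitment meeting and disclosed there, ahead of consent, baseline and the gap that held most of the attrition. None of the planned measures moves allocation for Baltimore. The consequence is a diluted as-randomised contrast: about 7.2 points instead of 15 if non-receivers gain nothing.

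The change is worth making in the one cohort still open, but it will not rescue the trial's power. At the lower bound it adds about 1 point of pooled power without replacement and about 4 points with 100 allocated; across the assumed range of 57 to 113 early losses, the gains are 1 to 2 and 4 to 13 points. All of this assumes that Unity's losses recur and that every early leaver goes before allocation. The benefit that does not depend on those assumptions is that consent and baseline would no longer follow knowledge of the arm.

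**What to change.** For the Baltimore cohort only:
- Replace assignment to arm-specific sessions with individual allocation.
- Take consent and baseline from all women at the recruitment meeting, before any arm is known.
- Show every woman the menu of circle times and record a slot she can attend.
- Generate and disclose the arm shortly before the first circle, after a confirming call to all women.
- State whether the 100 are counted at consent or at allocation, and report losses before allocation separately.
- Analyse with cohort or site as a stratum, because the Baltimore women and their allocation ratio will differ from Unity's.

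The cost is an amendment, a new allocation mechanism and a confirming call to every woman (facilitators already contacted participants in this interval). Some consented women will be lost before allocation; allocating 100 would take about 136 consents at the lower-bound loss. The Baltimore result will also apply to a somewhat narrower population, those able to start a circle.

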### Study population and eligibility criteria

We plan to recruit up to 440 AA women receiving care at Unity Health Care (Unity), a Federally Qualified Health Center (FQHC) in Washington, D.C. and Baltimore Medical System Incorporated (BMSI), a FQHC with practices in Baltimore, Maryland. Eligible patient participants include English-speaking women who self-identify as AA, are 40 to 75 years old, have uncontrolled hypertension (previously defined as systolic blood pressure ≥ 140 mmHg or diastolic blood pressure ≥ 90) [2, 25], and receive their primary care at a Unity Health Care practice or a BMSI practice. Participants will be randomly assigned to receive the PTSC intervention or usual care at Unity or Baltimore Medical System Inc.

Thus far, we have recruited 341 participants into the study (PTSC intervention arm = 216; usual care arm = 125; see Fig. 1), all of whom receive care at Unity Health Care and live in metropolitan Washington D.C. In the next phase of the study, we will recruit an additional 100 AA women residing in Baltimore, Maryland and receiving care at a BMSI practice. Of note, hypertension diagnosis guidelines have changed since the study’s inception, and hypertension is now defined as systolic blood pressure ≥ 130 mmHg or diastolic blood pressure ≥ 80 [25]. However, we are maintaining the same blood pressure thresholds as we had at the start of the study in order to maintain equivalence in evaluating program impact between cohorts over time, given that the previous hypertension diagnosis criteria were central to the study’s eligibility criteria and recruitment process. Moreover, the patients are currently being managed to meet the prior guidelines. Our criteria reflect the current designation for Hypertension Stage 2 [25].

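### Women learn their arm before they consent and before baseline is measured, so enrolment is open to selection by arm that the planned analysis does not remove

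*Protocol article*

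**What the plan says.** The order of events is in two consecutive parts of the protocol article.

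- **Assignment.** Recruitment and randomization: "Women are randomly assigned to attend a session designed for the treatment arm or the usual care arm".
- **Disclosure.** Same section: "Attendees learn of their assigned treatment arm after the presentations have been made".
- **Consent.** The next sentence: "At that point, written consent to participate in the study is obtained from those who wish to be a part of the trial".
- **Baseline.** Baseline data collection: "Upon consent, study participants complete a baseline survey"; and, in the same step, "Baseline measures of BP, waist circumference, height, and weight are also obtained".

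The only concealment described is that the randomising staff "are blinded to which sessions are for either arm, and both receive identical recruitment sessions".

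The Power calculation section plans 440 women, 220 per group. Study population and eligibility criteria reports enrolment to date as "PTSC intervention arm = 216; usual care arm = 125", with a further 100 women to come from Baltimore. The Discussion refers to the 216 as the women randomly assigned to the intervention.

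**The concern.** Joining the trial is a choice made after randomisation and with the arm known. A woman who came because the programme appealed to her can leave when she learns she has drawn usual care. A woman who cannot commit to 13 weekly sessions can leave when she learns she has drawn the programme. Either way, those who stay in one arm may differ from those who stay in the other in motivation, availability or health. Random assignment to sessions no longer protects the comparison of the women who are analysed.

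Baseline is also affected. Adherence, diet, physical activity and stress management are self-reported by women who already know what they will receive, and these answers form the baseline term of the difference-in-differences.

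At stake is the causal reading of every between-arm comparison, including the blood pressure outcome.

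**Working it through.** **1. Does baseline really follow disclosure?** For the survey, yes: it is placed after consent, and consent is placed after disclosure. For blood pressure and body measurements the order is inferred, because they are described in the same section immediately after the survey. The payments agree: $50 per data collection session and $200 for the recruitment session plus three follow-ups, i.e. 4 × $50. Baseline data are therefore collected at the recruitment session.

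**2. Does the stated blinding cover the consent decision?** No. It covers the staff who randomise and the content of the sessions. Both protections end when the arm is announced, and consent comes after that.

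**3. What allocation was planned?** No ratio is stated; 1:1 is inferred from 220 per group. The sample size fits equal groups. With 80% versus 65%, two-sided 0.05 and 1:1, the usual formula gives 151 per arm (302) at 80% power with continuity correction, or 310 to 316 at 85% power without it. The article's figure is 308, with no power level given. Its total of 440 equals 308/0.70.

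**4. How unusual is 216 versus 125 under 1:1?**
- Expected per arm: 341/2 = 170.5.
- z = (216 − 170.5)/√(341/4) = 45.5/9.23 = 4.93.
- Exact two-sided binomial p = 9.5 × 10⁻⁷.
- Intervention share: 216/341 = 63.3% (95% CI 58.0% to 68.5%).

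To finish at 220 per group, the remaining women would have to split 4 (220 − 216) versus 95 (220 − 125). If the next 100 split evenly, the totals would be 266 versus 175.

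**5. What else could produce the split?** It is compatible with assignment at 3:2 (p = 0.22) or 2:1 (p = 0.21). The binomial test also treats women as enrolling independently, whereas they attend in groups, so a poorly attended session could move the counts. The flow diagram (Fig. 1), which may give numbers by stage, was not available for this check.

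**6. Is lost power the main harm?** No. At 308 evaluable women and 80% versus 65%, power is 84.2% at 1:1 and 80.8% at the observed ratio. The issue is bias.

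**7. Does the planned analysis remove the bias?** The Analysis plan adjusts for sociodemographic characteristics, insurance, smoking and drinking, and chronic conditions. Motivation to change is not among them. Difference-in-differences removes stable differences in level between arms. It does not remove a difference in trend. For usual care, the bias is the mean change among women who consented minus the mean change among all women assigned, with the same term for the intervention arm. The text supplies neither quantity.

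**The case against.** The strongest case on the other side has four parts.

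- **Incentives to decline are softened.** The consent process is explained before the arm is revealed, sessions are identical, usual-care women may enter the programme at 15 months, and the data collection payments are described without distinction by arm. This stands as mitigation. It makes selection less likely but does not exclude it.
- **Measurement is partly protected.** Blood pressure is taken with a digital device under a set procedure, and utilisation comes from records. This stands: measurement with the arm known chiefly threatens the self-reports. It does not touch selection into the arms.
- **Attendance cannot depend on a known arm.** Women learn their arm only after the presentations, so if concealment holds, non-attendance is not a response to the arm. This stands. It means that part of the imbalance may come from session logistics and be harmless.
- **Baltimore may differ.** The sentence promising the same recruitment processes closes the paragraph on mailings and flyers, ahead of the one on randomisation. That the same consent order will apply is likely, not explicit.

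Two stronger readings are tempting. A reader might infer from 216 versus 125 that usual-care women refused in large numbers, so that the compared groups are demonstrably not the randomised ones. The documents do not support that, because unequal assignment or attendance could also explain the counts.

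A reader might also take the gap of 91 women (216 − 125; 91/216 = 42%) and compute a bias. If those women differed from the enrolled controls by 5 to 20 points in uncontrolled blood pressure, the usual-care proportion would move by 0.42 × 5 to 0.42 × 20, about 2 to 8 points. That needs equal numbers assigned and attending and an arbitrary difference, and it yields a shift in level. It is not the bias of a difference-in-differences estimate and should not be quoted as such.

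**Conclusion.** The concern holds as a defect of sequence. Consent and the baseline survey follow disclosure of the arm, so the enrolled groups are those who agreed to join knowing their arm. This is a risk of selection bias whatever caused the imbalance; it would remain with equal counts. The listed covariates and difference-in-differences do not remove it.

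The imbalance is supporting evidence only. Chance is an implausible explanation if allocation is 1:1 and women enrol independently, but both are assumptions. Differential consent is one of several possible causes. The size of any bias, and its direction, cannot be computed from the documents.

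**What to change.** **Baltimore cohort (about 100 women still to be recruited).** Within the same recruitment session, obtain written consent, complete the baseline survey and blood pressure, and only then reveal the arm. Count every consented woman as randomised in her arm. The Discussion says participants meet their facilitator at the recruitment meeting; that introduction should also come after the reveal.

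**First two cohorts.** The order cannot be changed. Stop describing the enrolled 216 simply as the women randomly assigned, and state that this comparison is subject to consent given after the arm was known. An effect by cohort can be shown as a sensitivity analysis. It should carry the note that the Baltimore estimate is imprecise and that the contrast is confounded with city, health system and the changes in programme delivery planned for the third cohort, so it cannot isolate the effect of consent order.

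**Cost.** An IRB amendment and a reordering of steps in sessions that are held anyway. Some women who would have declined on drawing usual care will now appear as attrition in that arm. That is a small price, since such losses become visible and can be counted.
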